## Methods

### Participants and procedure

The participants are a sample of 450 students aged 10–12 from primary schools in Southwest Finland. 150 children are refugees, 150 non-refugee immigrants, and 150 native-born Finnish schoolchildren. Schools are selected on the basis that they have a preparatory class where all asylum seekers and most non-refugee immigrants study for their first year after arriving in Finland. We will select one preparatory class and one regular class in each school to draft the sample for the study. The study has two time points: baseline measurements at the beginning of the school year (T_1_) and follow-up measurements at the end of the school year (T_2_). The study uses a screening battery tool to administer a variety of questionnaires and tests which are then used to give feedback about the students to teachers and multiprofessional student welfare bodies. We aim to collect all the data within one school year (2024–2025), but if the number of participants does not reach 150 in each group, a second round of data collection will take place in 2025–2026. We will conduct a small-scale pilot study in one preparatory and one regular class in Spring 2024.

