#### Analysis plan

**Power.** In order to form profiles across different groups of children and to assess changes in cognitive, social, and mental health functions across those children who will receive SB based supportive actions and those who do not, we performed a preliminary power analysis to determine the sample size required to detect medium-sized or larger effects on these primary outcomes. Based on typical sizes of Finnish preparatory classes, we estimated the average size of each cluster to be 17, with a variance of 10. Intraclass coefficients for these outcomes are challenging to estimate, but based on our previous cluster-randomized research among war-affected children, values of 0.01–0.1 could be reasonable. With a relatively conservative estimate of 0.07 for the ICC, and setting alpha at 0.05, to achieve 80% power to detect a medium-sized (d = 0.5) or larger effect, we would need about 150 children in each group, meaning approximately 450 children in total.

**Analyses.** Means, standard deviations, and correlations will be evaluated for all variables reported by children, parents, and teachers. To test Hypothesis 1, baseline differences between the study’s three groups will be investigated using 3-way ANOVAs and followed up with *t*-tests to compare means. To test Hypothesis 2, correlation analyses will first be used to examine whether mental health (trauma-related and depressive symptoms) is associated with poorer cognitive function and social competence. Latent profile analyses (using the TidyLPA package in R) will then be run for the entire sample under each of the three dimensions: cognitive, social, and mental health. Emerging profiles will be compared with how they line up with our three groups (refugee, immigrant, native-born Finnish).

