To test Hypothesis 3, screening battery effects on cognitive, social, and mental health functioning will be evaluated using repeated measures ANOVAs with 2 × 3 for {T_1_, T_2_} and {children who received SB-based support, children who received non-SB-based support, children who did not receive SB-based support} among children who scored above/under critical thresholds, and following up with *t*-tests to compare means. Differences in SB-based actions will also be evaluated qualitatively. We will further use linear regression to test whether changes in mental health (trauma- and depressive symptoms) and social functioning associate with changes in cognitive functioning from T_1_ to T_2_. In addition to analyses in the whole sample, we will also do these analyses by subgroup, separately for our three groups. Classroom atmosphere, teacher self-efficacy and awareness of culturally responsive education, family functioning, child language and development as well as children’s cultural background will be used as covariates in the regression analyses and ANOVAs. Effect sizes and confidence intervals will be reported for main effects and p-value based inference will be de-emphasized based on guidelines for New Statistics [60].

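### The sample size allows for clustering by class but the named tests do not, so the Hypothesis 1 intervals against native-born children may be too narrow (error about 11-12% instead of 5% if all clustering at ICC 0.07 is between classes)

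*Protocol article*

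**What the plan says.** All references are to the protocol article.

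- **Analysis plan, Power.** Classes are treated as clusters of average size 17 with variance 10. An ICC between 0.01 and 0.1 is considered reasonable, and the calculation proceeds "With a relatively conservative estimate of 0.07 for the ICC". The target is d = 0.5 with 80% power at alpha 0.05, which gives about 150 children per group and 450 in all.
- **Analysis plan, Analyses.** For Hypothesis 1, baseline differences between the "three groups will be investigated using 3-way ANOVAs and followed up with" t-tests. For Hypothesis 3, cognitive, social and "mental health functioning will be evaluated using repeated measures ANOVAs", again followed by t-tests. Associations between changes are tested by linear regression. Classroom atmosphere and teacher measures enter the ANOVAs and regressions as covariates. No random effect, multilevel model or cluster-robust error is mentioned. The Abstract lists the same family of methods.
- **Participants and procedure.** "We will select one preparatory class and one regular class in each school to draft the sample for the study". Preparatory classes hold all asylum seekers and most other immigrants in their first year after arrival.

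**The concern.** The power paragraph accepts that children in the same class resemble one another, and it more than doubles the sample for that reason. The tests named directly afterwards assume that the children are independent.

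This matters most for Hypothesis 1. If native-born children come from regular classes while refugee and most immigrant children come from preparatory ones, a comparison with native-born children is mainly a comparison of classes. A standard error computed as if there were 150 independent children on each side then leaves out the variance between classes. The intervals are too short and differences are declared too often. The planned emphasis on effect sizes and confidence intervals over p-values does not help, because the intervals use the same standard errors.

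Teacher and class covariates raise a related problem: one value is shared by a whole class but would be tested with child-level degrees of freedom.

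**Working it through.** **1. Reproduce the sample size.** Inputs from the Power paragraph: d = 0.5, alpha 0.05 (two-sided assumed), power 80%, ICC 0.07, cluster size 17, variance 10.

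- Independent children: 2 × (1.96 + 0.84)² / 0.5² ≈ 62.8, so 63 per group.
- Design effect: 1 + (17 − 1) × 0.07 = 2.12. With the cluster-size variance, 1 + ((1 + 10/289) × 17 − 1) × 0.07 = 2.16.
- Normal approximation: 62.8 × 2.12 = 133; 62.8 × 2.16 = 136.
- Cluster-level t calculation with 2(m − 1) degrees of freedom: m = 8.90 clusters (151 children) with equal clusters, or 9.05 clusters (154) with variance 10.

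The stated figure of about 150 is reproduced, but only if clustering is counted.

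**2. Layout implied by the sampling rule.** About 300 refugee and immigrant children in preparatory classes of 17 need 300/17 ≈ 18 classes. One regular class per school gives 18 regular classes. Each group then has 150/18 ≈ 8.3 children per class. The article does not state this number, so it is an assumption.

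**3. Error of an unadjusted test against native-born children.** Let ρ be the total ICC and ρc its class-level part, with k children of a group per class. School effects cancel in this contrast because both class types come from the same schools. The true variance divided by the variance that the test assumes is

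R = (1 − ρ) + k × ρc, and the actual two-sided error is 2 × (1 − Φ(1.96/√R)).

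| ICC | Class-level part | R (k = 8.33) | Error |
|---|---|---|---|
| 0.07 | all | 0.93 + 0.583 = 1.513 | 11.1% |
| 0.07 | half | 0.93 + 0.292 = 1.222 | 7.6% |
| 0.07 | none | 0.93 | 4.2% |
| 0.10 | all | 0.90 + 0.833 = 1.733 | 13.7% |
| 0.01 | all | 0.99 + 0.083 = 1.073 | 5.9% |

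Simulation of this layout agrees. At ICC 0.07 it gives 11.3-11.6% with all clustering at class level, about 7.5% with half at school level and about 4-4.5% with all at school level. At ICC 0.10, all at class level, it gives 13.7-14.0%. An error of 11-12% corresponds to a nominal 95% interval covering about 88-89%.

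**4. Other layouts at ICC 0.07, all at class level.** With 18 preparatory and only 9 regular classes, simulation gives about 15%. If each group filled its own classes of 17, R = 2.12 and the error is 17.8%.

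**5. Refugee versus immigrant.** In shared preparatory classes the class effect cancels, so R = 0.93 at ICC 0.07 and the error is 4.2% (simulated 4.0-4.6%). This contrast is slightly conservative.

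**The case against.** **The layout limits the size.** A reader might infer an error of 11-18% from the ICC and the class size of 17. The upper part of that range does not follow from the sampling rule. Equal numbers of preparatory and regular classes, with refugee and immigrant children sharing the former, lead to the 8-per-class layout. The 15-18% figures need about 9 regular classes of 17, or separate classes for each group. This objection stands.

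**The ICC may sit partly at school level.** The article does not split it, and the school part cancels. This also stands, and it makes the rate conditional.

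**Group and class type do not coincide exactly.** Some immigrants, and children past their first year, may be in regular classes. If 30% of refugee and immigrant children were (an assumption), the error at ICC 0.07 falls to about 7-8%.

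**Covariates may absorb class variance.** They may absorb some of it. They do not replace a class effect.

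**An article condenses.** A degrees-of-freedom method could be left to a fuller plan, and preregistration is still to come. Here, however, specific single-level tests are named beside a cluster-based sample size. That softens the point without removing it.

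**The same inflation everywhere.** A reader might apply these rates to every planned test. The article does not support this. For Hypothesis 3 and the change regressions, differences over time remove stable class effects, and any inflation depends on how far support and change vary by class. No rate is shown here for the correlations or latent profiles.

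**Conclusion.** The mismatch is real and lies within the article: the sample size allows for class clustering and the named analyses do not. For Hypothesis 1 contrasts with native-born children, the intervals would be too narrow whenever a material part of the ICC is between classes within schools.

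Under the stated sampling, the error of a nominal 5% test runs from about nominal (ICC 0.01, or all clustering at school level), through about 7-8% (ICC 0.07, half at school level), to about 11-12% (ICC 0.07, all at class level) and at most about 13-14% (ICC 0.10). These figures assume about 8 children of each group per class, two-sided tests, no help from covariates and complete separation of native-born from other children by class. Refugee versus immigrant is not inflated.

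The 3-way label is a minor wording slip: three groups form one factor, so it should read one-way.

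**What to change.** - **Hypothesis 1.** Use a linear mixed model with group as a single three-level factor, random intercepts for school and class, and small-sample degrees of freedom. Take the pairwise contrasts from that model. Cluster-robust errors with a small-sample correction are an acceptable alternative.
- **T1-T2 models.** Carry the class effect into the Hypothesis 3 and change analyses.
- **Teacher- and class-level covariates.** Test them on class-level degrees of freedom.
- **Wording.** Replace the 3-way label with one-way (three-group).

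The cost is a change of wording, best made in the planned preregistration. The child's class is already asked for under Tests and measures, and the research team selects the schools, so no new data are needed. The price is wider intervals for the native-born contrasts, which the sample size already anticipates.

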### Research question

First, we want to find out how the cognitive, social, and mental health functions of refugee children compare with (a) same aged immigrant children without refugee background and (b) native-born children in Finland. We will also examine whether worse mental health (trauma-related and depressive symptoms) is linked with poorer cognitive function and social competence across the sample. We hypothesize based on earlier (limited) literature in the field, 1) that refugee children, for whom exposure to trauma is likely more common, exhibit lower levels of cognitive functioning compared to immigrant children without refugee background and native Finnish children, and 2) that mental health problems and poorer social competence explain this link.

Second, we will examine whether reliable evaluation of cognitive, social, and mental health functions of students can inform schools about supportive actions for refugee children and whether this process is different compared with non-refugee immigrant children and/or native-born Finnish children. We will look at whether children who scored above/under critical thresholds on our Screening Battery (SB) report receive supportive actions during the school year. If they do, we look at what kinds of actions inside and outside the classroom schools conduct for refugee children, and whether the output of the SB was utilized to plan this support We will further look at whether the actions are different compared to actions with non-refugee immigrant children and/or native-born Finnish children and whether the actions are different compared to actions that do not use the information produced by the screening battery.

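### Hypothesis 2 says that mental health and social competence explain the refugee gap in cognition, but no planned analysis estimates how much of that gap they account for

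*Protocol article*

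**What the plan says.** The Protocol article's Research question section states two linked hypotheses. The first is that refugee children "exhibit lower levels of cognitive functioning compared to immigrant children without refugee background and native Finnish children". The second is "that mental health problems and poorer social competence explain this link". The same section asks, as a separate matter, whether worse mental health is "linked with poorer cognitive function and social competence across the sample".

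The Analysis plan then names the test of Hypothesis 2, in three steps:

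1. "correlation analyses will first be used to examine whether mental health (trauma-related and depressive symptoms) is associated with poorer cognitive function and social competence".
2. Latent profile analyses, which "will then be run for the entire sample under each of the three dimensions: cognitive, social, and mental health".
3. "Emerging profiles will be compared with how they line up with our three groups".

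Three other statements in the Analysis plan bear on the point:

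- Correlations are to be computed among all variables.
- A linear regression tests whether "changes in mental health (trauma- and depressive symptoms) and social functioning associate with changes in cognitive functioning" between the two time points.
- Analyses are to be repeated within each of the three groups. The covariates listed for the ANOVAs and regressions include neither symptom scores nor social competence.

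**The concern.** Hypothesis 2 concerns a difference between groups. It says that the cognitive gap arises because refugee children have more symptoms and poorer social competence. The article does not use the word mediation, but that is the natural reading of the hypothesis. The authors also keep it apart from the plain association question in the same section.

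The steps assigned to it answer the association question. The correlation relates symptoms to cognition and to social competence. In that step social competence, one of the two proposed explanations, appears as a correlate of mental health. Each latent profile model contains one domain only, so none links symptoms or social functioning to cognition. Comparing profiles with groups shows at most that the groups differ within each domain.

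Hypothesis 2 is the only hypothesis that addresses explanation, and the article's Discussion (in the Abstract) presents explaining underachievement as a main product of the study. If the plan stays as it is, that conclusion would rest on evidence that cannot establish it, and a suitable model added later would be post hoc.

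**Working it through.** **The plan's own figure.** The Power paragraph gives about 150 children per group (d = 0.5, 80% power, alpha 0.05 taken as two-sided, ICC 0.07, mean cluster size 17 with variance 10). An individually sampled comparison needs 63.8 per group (t-based). The design effect is 1 + ((1 + 10/289) × 17 − 1) × 0.07 = 2.161. The product is 138, or 9 whole classes of 17 = 153. A cluster-level t-test gives 151 to 154. The stated figure reproduces, but it is for a difference in means, not for an indirect effect.

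**What the planned correlation can show.** From the article: 150 of 450 children are refugees, so p(1 − p) = 1/3 × 2/3 = 2/9. Assumed, because the article gives no values:

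- the within-group SD of symptoms and of cognition is 1;
- the cognitive gap is G = −0.50, the size of the plan's d;
- refugee children's symptoms are shifted by a;
- the within-group slope of cognition on symptoms is b.

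Then:

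- Whole-sample correlation: r = (b + a·G·2/9) / √[(1 + a²·2/9)(1 + G²·2/9)]
- Explained part of the gap: a·b; explained share: a·b / G

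| Case | a | b | r | Share of gap explained | Simulation (2000 runs, 150 per group) |
|---|---|---|---|---|---|
| 1 | 0.8 | 0 | −0.089/1.098 = −0.08 | 0% | r −0.08, significant in 40% |
| 2 | 0 | −0.3 | −0.300/1.027 = −0.29 | 0% | r −0.29, significant in 100% |
| 3 | 0.8 | −0.3 | −0.389/1.098 = −0.35 | 0.24/0.50 = 48% | not run |
| 4 | 0 | −0.625 | −0.625/1.027 = −0.61 | 0% | not run |
| 5 | 0.8 | −0.625 | −0.714/1.098 = −0.65 | 0.50/0.50 = 100% | r −0.65, significant in 100% |

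The table shows the following:

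- Cases 2 and 5 both give a clear negative correlation, with 0% and 100% of the gap explained.
- Cases 4 and 5 have the same within-group correlation, −0.625, and nearly the same whole-sample correlation. The explained shares are again 0% and 100%. Correlations computed within each group therefore do not settle the matter.
- Cases 3 and 5 both meet the two conditions that the plan checks (symptoms related to cognition, groups differing in symptoms). The shares are 48% and 100%.

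With one explanatory variable, a reader could multiply a and b by hand. Hypothesis 2 names several (trauma symptoms, depression, social competence). If these are correlated, products of pairwise slopes count the shared part more than once, so a joint model is needed.

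**Other analyses in the article.** The regression concerns change over the school year, not the baseline gap. The ANOVA covariates leave out the proposed explanations. No stated model contains group, explanatory variables and cognition together.

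**The case against.** The planned steps are relevant to Hypothesis 2. A reader might infer that they can neither support nor refute it, or that background group never enters. Both go too far. The profiles are compared with the groups, and the baseline group comparisons are not clearly limited to cognition, so cases 2 and 4 would be likely to show up as no group difference in symptoms. A near-zero correlation would also count against the hypothesis, barring suppression.

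A reader might also infer that any negative correlation would be declared support. The article states no such rule. The correlation comes first in a sequence, and the plan favours effect sizes and intervals over p-values.

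Confounding by group is a limited worry too. With no within-group association and a 1 SD gap on both variables, r = −(2/9)/(1 + 2/9) = −0.18. With gaps of 0.5 SD it is −(0.25 × 2/9)/(1 + 0.25 × 2/9) = −0.05, below the roughly 0.09 (1.96/√450) needed for significance without clustering. The by-subgroup analyses would remove this confounding if they extend to the correlations, which the text leaves unclear.

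Social competence is not only a correlate of mental health. The all-variable correlations pair it with cognition, and the change regression includes social functioning, which goes some way towards the interplay aim.

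All of this stands as a limit on the criticism. None of it supplies an estimate of the explained share of the gap.

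**Conclusion.** The point holds in limited form. The analyses named for Hypothesis 2 address necessary conditions, and nothing in the Analysis plan estimates whether, or how much, mental health and social competence account for the baseline gap. A clear negative correlation is compatible with 0% and with 100% of the gap explained.

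This is not detail left to a fuller plan. The article names the test, and the test answers a different question.

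The numbers rest on assumed path values and an assumed gap of 0.50 SD, and the simulation ignores class clustering. The logical point does not depend on those values. This should be fixed before preregistration. It does not affect recruitment or measurement.

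**What to change.** On T1 data, regress each cognitive outcome, or a prespecified composite, on group, first without and then with trauma symptoms, depression and social competence. Report the change in the gap (the indirect effect) for refugee versus non-refugee immigrant children and for refugee versus native-born children, with confidence intervals that allow for clustering by class. Group, explanatory variables and outcome are measured together, so the wording should be that these variables statistically account for part of the gap, not that they cause it.

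Keep the correlations as description, and state whether the by-subgroup analyses include them. Cross-classify the three sets of profiles, so that the interplay between domains is examined directly.

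The alternative is to reword Hypothesis 2 as an association, which the planned correlations can address.

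The cost is modest extra analysis on variables already collected. The drawback is precision: about 150 per group was not derived for indirect effects, and power for them cannot be computed without path values that the article does not give. Intervals may be wide, and the plan should say so.

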**Methods:**

Four hundred fifty children aged 10–12 will be recruited from primary schools, including 150 children of refugee background, 150 of non-refugee immigrant background, and 150 native-born Finnish children. A screening battery including tasks and questionnaires on different aspects of cognitive, social, and mental health functioning will be used to assess the children in their classrooms at the start and end of a school year. Supporting information will also be collected from parents and teachers. The information gathered will be collated into class-level feedback reports for teachers and, with parental permission, individualized reports for multiprofessional student welfare bodies, for informing supportive actions. Correlational and latent profile analyses, ANOVAs, and linear regression will be used to answer the research questions.

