### Screening battery

The screening battery (SB) gathers many kinds of data about the participants using demographic survey questions, tasks, and questionnaires. The children answer questions and complete tasks, and data is also collected from parents and teachers. The battery contains standardized and universally applicable assessments of a) cognitive functions (general intelligence, working memory, self-regulation, and self-efficacy and decision making), b) mental health (symptoms and well-being), and c) social competence. Prior to T_1_, the research group will offer a half-day training to teachers and school psychologists participating in the study on how to use the screening battery and specifically its feedback function. During the training, initial ideas and resources on how to transform the feedback into supportive actions at schools will be discussed among participating teachers and school psychologists.

The screening battery uses the Gorilla online platform to administer questionnaires and tasks (https://gorilla.sc/). Results are then transferred via an API to a Microsoft Power BI feedback tool which compiles both anonymous general (for teachers) and personalized (for multiprofessional student welfare bodies with consent from children’s parents) feedback with data visualizations and recommendations for supportive measures for students. At the end of the school year, the SB is administered again for the same classes (T_2_). The data about any supportive actions (either using the information produced by SB or not) that children may have received during the school year is also collected. The data is collected from parents, teachers, and multiprofessional student welfare bodies. The child’s own experiences of the support received are also collected during follow-up measurements. The researchers, who are all licensed psychologists and specialists in child cognitive and social skills as well as in child mental health, will be available for consultations with the schools throughout the study year, in case the school has further questions or concerns.

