### Feedback tool

The feedback tool collates information on participants’ cognitive, social, and mental health functioning and compiles two reports: one for the teacher and one for school health staff. The teacher report is at a classroom level and presents results as anonymized averages. The teacher data includes a categorical graphical representation (“low”, “average”, “high”) of self-regulation, intelligence, self-efficacy, resilience, depression, trauma, loneliness, altruism, and language development levels in the classroom, with clarifying depictions of these qualities and guidance for their interpretation written by clinical psychologists working in the research project. The school health service report involves individual student data. Upon request, and with the permission of the parents, the multi-professional student welfare body is offered detailed data on the individual’s results on the screening battery. This includes a graphical summary of cognitive, social, and mental health data gathered in the study compared to subsample means (refugee, immigrant, native Finnish) for each child on each variable. The individual results can also be discussed with the child him/herself.

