#### Teacher report

**Teacher self-efficacy** in the classroom is measured by Teachers’ Sense of Efficacy Scale (TSES). The TSES is a 12-item questionnaire, where teachers indicate on a 9-point scale how much they can do as teachers in each of the situations described (1 = *nothing*, 3 = v*ery little*, 5 = s*ome influence*, 7 = *quite a bit*, 9 = *a great deal*).

**Teachers' view of children’s co-operation skills and classroom atmosphere.** This quality is measured with a 9-item questionnaire developed in the Yhteispeli project in Finland [57]. Teachers respond on a 5-point scale how well the statements fit him/her.

At T_2_, we collect information on whether or not the information provided by the SB has been used and a list of supportive actions in the classroom.

**Teachers’ beliefs and perspectives on teaching for social justice** are measured with nine items of the original 12-item Learning to Teach for Social Justice-Beliefs (LTSJ-B) scale [58], because the nine-item adaptation has previously been adapted and found suitable for the Finnish school context [59]. The teachers assess items related to culturally responsive education on a five-point scale (1 = s*trongly agree*, 2 = a*gree*, 3 = *I don’t know*, 4 = d*isagree*, 5 = s*trongly disagree*).

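### Screening battery feedback works at class and at child level, but Hypothesis 3 uses one child-level exposure factor, and either way of coding class-wide use weakens the contrast

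*Protocol article*

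**What the plan says.** All references are to the Protocol article.

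- **Two levels of feedback.** The abstract's Methods paragraph says: "The information gathered will be collated into class-level feedback reports for teachers and, with parental permission, individualized reports for multiprofessional student welfare bodies". Under Feedback tool, "The teacher report is at a classroom level and presents results as anonymized averages", while for individual results "Upon request, and with the permission of the parents, the multi-professional student welfare body is offered detailed data on the individual’s results".
- **Who is exposed.** Under Screening battery, before T1 "the research group will offer a half-day training to teachers and school psychologists participating in the study". Under Participants and procedure, "We will select one preparatory class and one regular class in each school to draft the sample for the study". No class or school without SB feedback is described.
- **What counts as support.** The Research question section asks about actions both in and out of the classroom. Hypothesis 3 is that actions informed by the SB work better than other actions; it is not limited to actions based on an individual report.
- **What is recorded at T2.** Under Teacher report, teachers state "whether or not the information provided by the SB has been used and a list of supportive actions in the classroom". Under Parental report, the parent states whether SB information was used for the child. The Screening battery section adds reports on supportive actions from the welfare bodies.
- **How it is analysed.** Under Analysis plan, Hypothesis 3 is tested by a 2 × 3 repeated measures ANOVA among children beyond the thresholds. The three-level factor is: "children who received SB-based support, children who received non-SB-based support, children who did not receive SB-based support".

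**The concern.** The intervention and the T2 reports have two levels, but the analysis factor has one. Consider a child whose individual report was never requested, in a class whose teacher used the class report to plan classroom work. The single factor must put this child somewhere, and neither place is satisfactory. As a comparison child, the child may carry part of the exposure under test. As an SB-supported child, the child shares that label with every classmate and with children whose own results were acted on.

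Hypothesis 3 is the plan's test of whether SB-informed support works better than other support. Under the first coding, a small or null difference could mean no benefit or a contaminated comparison group. Under the second, a difference could reflect the teacher or the class rather than the SB.

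**Working it through.** **1. The two possible codings side by side**

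| Child's situation | Classroom SB use counts as SB-based | Classroom SB use does not count |
|---|---|---|
| Teacher used class report, individual report used | SB-supported | SB-supported |
| Teacher used class report, no individual report used | SB-supported | Comparison, although reached by SB-informed classroom actions |
| Teacher did not use class report, individual report used | SB-supported | SB-supported |
| Neither used | Comparison | Comparison |

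In the left column there is no dilution, but every child in a class with SB use has the same exposure, and rows 1 and 2 are merged. The listed covariates (classroom atmosphere, teacher self-efficacy and attitudes) capture some differences between classes, but class itself is not a term in the stated ANOVA. In the right column the comparison group contains row 2.

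If the left column applies, precision comes from the number of classes. Assuming 17 participants in every class, 450 / 17 is about 26 classes in total, before restriction to children beyond the thresholds.

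**2. The plan's own sample size**

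Inputs from the Power paragraph: d = 0.5, alpha 0.05 (two-sided assumed), power 80%, ICC 0.07, mean cluster size 17, variance 10.

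- Unclustered: 2 × (1.96 + 0.84)² / 0.5² = 62.8, so 63 per group.
- Design effect: 1 + [17 × (1 + 10/17²) − 1] × 0.07 = 1 + 16.588 × 0.07 = 2.161.
- 63 × 2.161 = 136.2, so 137 per group. Rounded up to whole classes this is 9 × 17 = 153; a noncentral t calculation with class-level degrees of freedom gives 154. Both are close to the stated 150.

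The figure reproduces approximately and has no allowance for contamination.

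**3. Illustration of dilution under the right-hand coding**

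Let c be the share of comparison children in classes whose teacher used the SB report, and f the fraction of the effect carried by classroom actions. The document gives neither. The formula also assumes that every SB-supported child receives the classroom component, which is not true of row 3.

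Observed d = 0.5 × (1 − c × f). Power uses a normal approximation with 150 per group and design effect 2.161, so the standard error is √(2 × 2.161 / 150) = 0.170.

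| c | f | Observed d | Power |
|---|---|---|---|
| 0 | any | 0.50 | 84% |
| 0.25 | 0.25 | 0.47 | 79% |
| 0.50 | 0.50 | 0.375 | 60% |
| 0.75 | 0.50 | 0.31 | 45% |

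The 150 refers to the refugee, immigrant and native-born groups. The Hypothesis 3 groups are subsets of unplanned size, so the power column shows sensitivity to dilution and is not a forecast.

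**The case against.** The strongest reply is that the article does not say classroom actions are excluded. Since it counts classroom actions as support and asks teachers about SB use together with classroom actions, the natural reading is that an SB-informed classroom action is SB-based support. Dilution then does not arise. How the child, parent, teacher and welfare-body reports are combined may also be set out in the full protocol or the preregistration.

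This stands as far as it goes. A reader might infer that comparison children do receive SB-informed actions and that the contrast is therefore biased towards no difference. The document does not support that:

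- Receiving a class report is not the same as using it; use is something the study measures at T2.
- Support is observed rather than allocated. Need, parental permission and staff engagement may all influence who gets SB-based support, so the net bias could go either way.
- The 0.5 is the effect the study is sized to detect, not a known true effect, and c and f are assumptions.
- That the teacher gives one answer for the whole class is inferred from the wording of the item, not stated.

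The reply does not remove the point, because the article does fix a single three-level factor. A coding rule held elsewhere could only choose between the two columns above, and the column without dilution brings confounding with class and teacher and merges two kinds of support.

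**Conclusion.** The point holds in conditional form. One child-level factor cannot represent an exposure that acts at both class and child level. Depending on the coding, the Hypothesis 3 contrast is either open to dilution or largely a comparison between classes. The values d = 0.31 to 0.47 rest entirely on assumed c and f and on full classroom exposure of SB-supported children; they show that dilution could matter, not that it occurs. Neither the direction nor the size of the net bias can be established from the document.

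The three labels also overlap as worded: children with non-SB-based support are contained in those without SB-based support. Making the labels exclusive is needed but does not by itself resolve the two-level problem.

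**What to change.** Before the T2 data are coded:

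1. Code SB exposure as two factors: (a) class-level SB use, from the teacher's T2 report; (b) SB information used for the individual child, from the parent's T2 item and the welfare body's report. State how disagreement between these sources is resolved.
2. Make the support categories mutually exclusive, separating non-SB support from no support.
3. Enter both factors in the Hypothesis 3 model and report both effects. Testing only the child-level factor would narrow the hypothesis, which covers any SB-informed action. State that the class-level effect is a between-class comparison with class-level precision.
4. Add a sensitivity analysis whose comparison children come only from classes where the teacher reports no SB use.

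The cost is recoding of data already planned, one extra model term and one extra analysis; no further recruitment is needed. The downsides should be stated. The sensitivity analysis uses fewer children and remains confounded with class and teacher. The parent item will be incomplete, since the Parental report section expects that some parents will not be reached. None of this removes selection into support, which remains a limitation of the observational contrast.
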